## Abstract

**Background:**

Stroke patients usually suffer primary cognitive impairment related to attention, memory, and executive functions. This impairment causes a negative impact on the quality of life of patients and their families, and may be long term. Cognitive rehabilitation has been shown to be an effective way to treat cognitive impairment and should be continued after hospital discharge. Computerized cognitive rehabilitation can be performed at home using exercise programs that advance with predetermined course content, interval, and pace. We hypothesize that computerized rehabilitation might be improved if a program could customize course content and pace in response to patient-specific progress. The present pilot study is a randomized controlled double-blind crossover clinical trial aiming to study if chronic stroke patients with cognitive impairment could benefit from cognitive training through a customized tele-rehabilitation platform (“Guttmann, NeuroPersonalTrainer”^®^, GNPT^®^).

**Methods/design:**

Individuals with chronic-stage stroke will be recruited. Participants will be randomized to receive experimental intervention (customized tele-rehabilitation platform, GNPT^®^) or sham intervention (ictus.online), both with the same frequency and duration (five sessions per week over 6 weeks). After a washout period of 3 months, crossover will occur and participants from the GNPT^®^ condition will receive sham intervention, while participants originally from the sham intervention will receive GNPT^®^. Patients will be assessed before and after receiving each treatment regimen with an exhaustive neuropsychological battery. Primary outcomes will include rating measures that assess attention difficulties, memory failures, and executive dysfunction for daily activities, as well as performance-based measures of attention, memory, and executive functions.

**Discussion:**

Customized cognitive training could lead to better cognitive function in patients with chronic-stage stroke and improve their quality of life.

**Trial registration:**

NCT03326349. Registered 31 October 2017.

**Electronic supplementary material:**

The online version of this article (10.1186/s13063-018-2577-8) contains supplementary material, which is available to authorized users.

## Background

Stroke, the most common cerebrovascular disease, is a focal neurological disorder of abrupt development due to a pathological process in blood vessels [1]. There are three main types of stroke, namely transient ischemic attack, characterized by a loss of blood flow in the brain and which reverts in less than 24 h without associated acute infarction [2]; ischemic stroke, characterized by a lack of blood reaching part of the brain due to the obstruction of blood vessels and causing tissue damage (infarction), wherein cells die in the immediate area and those surrounding the infarction area are at risk; and a hemorrhagic stroke, where either a brain aneurysm bursts or a weakened blood vessel leaks, resulting in blood spillage into or around the brain, creating swelling and pressure, and damaging cells and tissue in the brain [3].

In 2013, according to the World Health Organization (WHO) and the Global Burden of Disease study, worldwide, there were 11–15 million people affected by stroke and almost 1.5 million deaths from this cerebrovascular disease [4, 5]. Moreover, in 2013, the total Disability-Adjusted Life Years (years of healthy life lost while living with a poor health condition) from all strokes was 51,429,440. In Spain, in 2011, the National Institute of Statistics reported 116,017 cases of stroke, corresponding to an incidence of 252 episodes per 100,000 inhabitants [6]. Although stroke incidence increases with advancing age, adults aged 20–64 years comprise 31% of the total global incidence.

Stroke often results in cognitive dysfunction, and medical treatment may cause great expense on a personal, family, economic, and social level. Depending on the area of the brain affected and the severity of lesions, stroke patients may suffer cognitive impairment, and alteration in emotional and behavioral regulation [7]. Generally, cognitive impairment derived from stroke includes alterations in attention, memory, and executive function [8].

Recent reports have begun to show positive results from the use of computerized cognitive rehabilitation systems (CCRS) for stroke patients to improve attention, memory, and executive functions. Nevertheless, more research is needed to better control variables and improve training designs in order to reduce heterogeneity and increase control of the intensity and level of performance during treatments [9–12].

CCRS allow adjustment of the type of exercises administered to the specific cognitive impairment profile of each patient, but within a fixed set of possible exercises such that heterogeneity of therapy choice is minimized. This can improve studies by allowing better categorization of patient groups that execute similar training sessions in a similar range of responses [13]. Further, CCRS offers the possibility of applying cognitive rehabilitation at home, while patient adherence and performance can be monitored online, so that patients do not need to live near, lodge near, or travel to a rehabilitation center to receive therapy. Because CCRS therapy is entirely digitized, it generates objective data that can be analyzed to determine the relative effectiveness of these interventions. We hypothesize that by allowing a trained professional to oversee an automated customization program that stratifies the level of difficulty, duration, and stimulus speed of presentation, we will reduce the heterogeneity of traditional cognitive training and improve the efficacy of intervention in chronic stroke patients.

The first objective of this pilot study is to assess if chronic stroke patients with cognitive impairment could benefit from cognitive training through a customized tele-rehabilitation platform (“Guttmann, NeuroPersonalTrainer”^®^, GNPT^*®*^) [14] intended to increase the control of experimental variables (cognitive impairment profile, adherence, and performance) traditionally identified as a source of experimental heterogeneity. The study aims to assess if this benefit could translate into an improvement of the trained cognitive domains (attention, memory, and executive functions).

The second objective is focused on generalization, namely the ability to use what has been learned in rehabilitation contexts and apply it in different environments [15]. Transfer of learning is included within the concept of generalization when specifically referring to the ability to apply specific strategies to related tasks [16]. Two types of transfer have been proposed – near transfer and far transfer [17]. By near transfer we mean that, through the training of a task within a given cognitive domain, improved function in other similar, untrained tasks may be observed in the same cognitive domain. For instance, a patient who performs selective attention exercises and improves execution through the training might improve their performance in other selective attention exercises too. By far transfer we mean that training in a given cognitive domain may improve performance of tasks in other cognitive domains. Such improvement will be observable in tasks that are structurally dissimilar from the ones used in the training. For instance, if a patient performs selective attention exercises, they may also improve their performance in memory tasks.

It has been demonstrated that computerized cognitive training can lead to the phenomenon of transfer, as previously studied in stroke patients [18]. Thus, our research aims to note whether the application of patient-customized tele-rehabilitation can give rise to an improvement in other functions that are based on cognitive domains related to those that have been trained (near transfer) as well as in different ones (far transfer).

Finally, the third objective is to assess the variables of demography (age, sex, years of education) and etiology (ischemic stroke or hemorrhage) and their impact on rehabilitation outcome, given the need to understand the patient characteristics that may influence treatment effectiveness [19].

## Methods

### Design

The present pilot study is a double-blind, randomized, crossover clinical trial with two arms (Figs. 1 and 2, SPIRIT). Participants will be randomly assigned to either experimental intervention (GNPT^®^) or sham intervention (ictus.online). In the first phase, participants in group A will start with the experimental intervention over a 6-week period (30 sessions), and participants in group B will start with the sham intervention over the same 6-week period (30 sessions). Participants will connect from their homes with their computer to the assigned intervention (experimental intervention or sham intervention). It will be indicated to them to connect once a day, from Monday to Friday, for 6 weeks. After a 3-month washout period, the second phase will commence, in which the groups will be crossed over, namely group A will receive the sham intervention and group B will receive the experimental intervention for 6 weeks each.

**Fig. 1 Fig1:**
[figure not shown]
Study flow diagram

**Fig. 2 Fig2:**
[figure not shown]
SPIRIT figure: schedule of enrolment, interventions and assessments

Evaluations will be conducted pre- and post-training by the study examiner. The examiner will be blind to the allocation of participants. Pre-testing will occur immediately before starting training (A1), and post-testing will occur immediately following both experimental and sham interventions (A2/A4) and after the 3-month washout period (A3). A follow-up neuropsychological assessment will be performed 6 months after treatment has terminated (A5).

A study researcher blinded to assessment procedure will perform the randomization of participants using the rand() function of Microsoft Excel software (Microsoft Excel 2010 for Windows), which is considered a good tool of randomization, having passed the Diehard test [20]. Each participant will have a “list entry” in our database, meaning that they will be stratified based on the two variables of interest in our study – sex (male or female) and type of stroke (ischemic or hemorrhagic). The rand() function will then assign random numbers from 0 to 1 to the stratified sample. The random numbers are ordered from lowest to highest and the first half of the list is assigned to group A and the second half to group B. A study researcher will create a letter with the information of the intervention to be performed (GNPT^®^ or ictus.online) for each participant and will place it in a sealed envelope. The examiner will deliver the sealed envelope to each participant when the first and the third neuropsychological examinations (A1 and A3) take place.

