### Sample size

This is study will be an explorative pilot study. The total sample size required for a two-arm trial following some currently proposed approximation guidelines is between 24 and 70 [21]. Some recently published studies similar to this one have used sample sizes within this range [22–24]. The aim is to recruit 40 participants (*n* = 20 per group). The results of this pilot study will be used to compute sample size and conduct a power calculation to plan a full-scale study.

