#### Statistical analysis

##### Analysis

Data analysis will be based on the intention-to-treat principle, which means that all participants who were randomized will be included in the final analysis, regardless of their adherence to any of the interventions. To avoid the problems derived from missing data (no attendance to neuropsychological assessments), blank spots will be filled with missing data imputation technique last value carried forward.

In order to detect changes in the variables recorded for the primary outcome and secondary outcome, a within-subject comparison pre-/post-intervention in both groups after both interventions will be made, as well as comparisons between groups (group A and group B).

Our null hypothesis is that a difference between baseline scores (A1 for group A and A3 for group B) and scores post-treatment (A2 for group A and A4 for group B) will not be significantly different from zero. Therefore, the Kolmogorov–Smirnov test will be used to examine the data for normality, and either ANOVA (parametric test) or Kruskal–Wallis (non-parametric test) will be used to analyze the measurements. A significance level of 95% will be used (*P* < 0.05 cutoff). Demographic (age, sex, years of education) and etiologic characteristics (ischemic stroke or hemorrhage) will be described using descriptive statistics for each group (group A and group B). The Bonferroni method will be applied to adjust the overall level of significance for multiple outcomes.

Alternatively, composite indices will be created by transforming raw neuropsychological test scores into z scores using published normative data. Domains will be created by averaging the z scores for each test within the domain (M = 0; SD = 1). This system has been used before in similar studies [44, 45].

If the sample size of this pilot study allows, a longitudinal mixed model will be applied.

Data analysis will be performed by an analyst outside the study with the statistical analysis software R and appropriate packages (“lmm” and “psych”) [46].

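### The group A versus group B comparison names no adjustment for the baseline score or the stratification factors; ANCOVA would be modestly more efficient

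*Protocol article*

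**What the plan says.** In the Design section, participants are "stratified based on the two variables of interest in our study", which are sex and type of stroke. Random numbers are then attached to the stratified sample and sorted, and "the first half of the list is assigned to group A and the second half to group B". The text does not say whether the halving is done inside each of the four strata or once over the whole list.

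The Statistical analysis section plans within-subject pre/post comparisons, "as well as comparisons between groups (group A and group B". The named tests are ANOVA or Kruskal–Wallis, chosen after a normality test. Sex and stroke type appear there only among characteristics to be summarised descriptively, although the Background makes their influence on outcome the third objective. The null hypothesis concerns the pre-to-post difference over the GNPT period of each group (A1 to A2 in group A, A3 to A4 in group B). A longitudinal mixed model is to be used if the sample size permits; its terms are not listed.

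Under Sample size, "The aim is to recruit 40 participants", 20 per group. No power is claimed.

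**The concern.** The factors that shape the randomisation, and that the third objective treats as relevant to outcome, are in none of the stated comparisons. The main effects of sex and stroke type cancel in within-person contrasts, but an A-versus-B comparison is between persons. The first-period comparison of the two groups is also the randomised contrast that carry-over cannot touch, and it rests on only 20 per group.

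Two kinds of precision may be lost. First, a change score uses the baseline value less efficiently than a covariate does. Second, if allocation is balanced within strata and the factors predict outcome, leaving them out counts balanced variation as error. The article also says "The results of this pilot study will be used to compute sample size and conduct a power calculation to plan a full-scale study", so a variance larger than necessary could carry over into the size of the next trial.

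**Working it through.** **Inputs from the article.** 20 per group; significance cutoff 0.05. The sides of the test are not stated, and two-sided is assumed here. The planned Bonferroni adjustment is left out for simplicity.

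**Assumed, because the article gives no figure.** Equal SD of 1 before and after; pre-post correlation rho from 0.5 to 0.9; effect of 0.5 SD (0.6 SD in the simulation); share of variance explained by the strata (R²) from 0.02 to 0.20.

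**Stated figure.** There is no power, effect size or SD, so 40 cannot be reproduced by a power calculation. 20 + 20 = 40 does lie in the cited range of 24 to 70. For orientation, an unadjusted comparison of 20 with 20 has 80% power for (1.96 + 0.842) × √(2/20) = 0.89 SD.

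**Step 1: baseline as covariate or as change score.** Residual variance is 1 for a post-only comparison, 2(1−rho) for a change score and 1−rho² for ANCOVA. ANCOVA therefore leaves 1−rho² of the post-only variance and (1−rho²)/[2(1−rho)] = (1+rho)/2 of the change-score variance. Power is Φ(0.5/(s√(2/20)) − 1.96), with s the residual SD. Post-only power is 35% throughout.

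| rho | ANCOVA / change variance | SE ratio, change / ANCOVA | Power, change | Power, ANCOVA |
|---|---|---|---|---|
| 0.5 | 0.75 | 1.155 | 35% | 45% |
| 0.7 | 0.85 | 1.085 | 53% | 60% |
| 0.9 | 0.95 | 1.026 | 94% | 95% |

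A later trial sized on the change-score variance would need 2/(1+rho) times the number that ANCOVA needs, for example 2/1.7 = 1.18 at rho 0.7.

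**Step 2: strata in a post-only comparison, balanced within strata.** The SE ratio, unadjusted to adjusted, is 1/√(1−R²). For R² of 0.02, 0.05, 0.10 and 0.20 it is 1.01, 1.03, 1.05 and 1.12, and power goes from 35% to 36%, 37%, 39% and 42%.

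**Step 3: strata once baseline is used.** Simulation of 4,000 trials of 40, with rho 0.7, effect 0.6 SD and strata explaining 10% of baseline variance. In the rows below, the strata explain 0%, 10% or 20% of what baseline leaves unexplained. Monte Carlo error is about √(0.7 × 0.3/4000) = 0.7 points for power and √(0.05 × 0.95/4000) = 0.3 points for size.

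| Split | Residual explained | Change | Change + strata | ANCOVA | ANCOVA + strata |
|---|---|---|---|---|---|
| Within strata | 0% | 68% | 68% | 73% | 73% |
| Within strata | 10% | 71% | 72% | 74% | 77% |
| Within strata | 20% | 73% | 76% | 76% | 82% |
| One list | 0% | 67% | 66% | 73% | 70% |
| One list | 10% | 70% | 69% | 72% | 74% |
| One list | 20% | 71% | 73% | 73% | 79% |

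**Step 4: are unadjusted standard errors too wide?**
- Within-strata split, 20% of residual: the change-score SE is 0.231 to 0.232 against a true SD of 0.220 to 0.226, so 2% to 5% too wide, with type I error 4.0%. ANCOVA without strata has 0.225 to 0.226 against 0.207 to 0.212, so 6% to 9% too wide, with type I error 3.7%.
- Within-strata split, 10% of residual: unadjusted type I errors were 5.2% (change) and 5.0% (ANCOVA), so no conservatism showed.
- One list, 20% of residual: the change-score SE is 0.230 against 0.231 to 0.232, with type I error 5.3%. The standard errors are correct.

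**The case against.** The strongest reply is that the plan does use baseline. Its null hypothesis is about change, so a reader who infers that the comparison ignores the baseline score goes further than the text allows. That largely stands. The hypothesis describes the GNPT periods and not the A-versus-B contrast, so the way baseline enters the latter is unstated; but change is the only quantity named, and the fair comparison is ANCOVA against change.

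A reader might also infer that the stated tests are plainly too conservative. In a post-only test with four equal, balanced strata explaining 10%, 20% or 30% of outcome variance, the nominal 5% test has true size 3.8%, 2.8% or 2.0%, and power for 0.8 SD is 70%, 71% or 71% unadjusted against 74%, 78% or 83% adjusted. The article supports neither the post-only analysis nor those R² values, and it does not establish the within-stratum split. If the strata shift only the level of the score, change scores in the same setting have size 4.8% to 5.2% without the strata, and adding them moves power by 0.3 points or less.

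Finally, covariate lists commonly sit in an analysis plan, which is not shown here, and the conditional mixed model might carry these terms. That stands as a reason for low severity. It does not dispose of the point, because the article does name the tests, and Kruskal–Wallis has no place for a covariate.

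**Conclusion.** Minor: a cheap gain in efficiency, not an error. The firmer part is baseline ANCOVA. Against change scores, the change-score SE is 3% to 15% larger for rho 0.9 to 0.5, assuming equal variances before and after. The strata part is conditional. It needs sex and stroke type to predict outcome beyond baseline, and standard errors are conservative only if the split is balanced within strata. The effect is then about 5% in SE for a post-score comparison at R² 0.10, and near zero for change scores if the strata shift only score level. The correlation, effect size and R² are all assumed.

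It would be wrong to infer bias, an inflated type I error or a missed power target. None follows: any distortion is in the conservative direction, and the study presents itself as an exploratory pilot with no power claim to contradict.

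**What to change.** In the Design section, state that the random split is made within each sex-by-stroke-type stratum.

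In the Statistical analysis section, replace the unadjusted ANOVA or Kruskal–Wallis for A versus B with a linear model (ANCOVA) for each outcome, containing group, the A1 value of the same measure, sex and stroke type. If the mixed model is fitted, include the same terms as fixed effects.

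The cost is two sentences and three degrees of freedom (residual 40 − 2 = 38 becomes 40 − 5 = 35). All the variables are already collected. If the strata turn out not to be prognostic, their terms cost a little power: essentially nothing in the simulation with a within-strata split, and about 3 points (73% to 70%) if one list is halved. That is a further reason to settle the allocation wording.

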### Intervention

#### Experimental intervention

GNPT^®^ is a tele-rehabilitation platform that allows therapists to configure and schedule rehabilitation sessions, consisting of a set of personalized computerized cognitive exercises. The examiner from the study will perform the initial neuropsychological assessment and the results of this assessment will be stored in the GNPT^®^ system by a study researcher. The program will then calculate a cognitive profile using these results, taking into account the patient’s age and educational level. Using this profile, the program will assign a set of computerized tasks to a certain day, configuring the input parameters of each task in order to personalize treatments. The neuropsychological assessment done at A1 (for group A) and A3 (for group B) will be used to establish the cognitive profile. Starting from each patient’s initial cognitive capacity, therapeutic plans will be adjusted to the level of execution and adapted to the patient’s evolution according to the obtained results. The adjustment is performed by GNPT^®^ using an automated process. The difficulty level of the tasks will vary and will be adapted according to the participant’s performance. Once a rehabilitation session is defined, the participant executes the assigned tasks, sending the results back to the server located at Institut Guttmann, such that therapists can asynchronously see the performance. A researcher from the study group will be exclusively dedicated to supervising this process.

The treatment consists of a set of 1-h sessions, five sessions per week during 6 weeks. A series of cognitive exercises of attention, memory, and executive functions will be conducted in each session (Fig. 3).

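### The blinded examiner is made the courier of the letter naming the intervention, which puts the assessor blind at avoidable risk

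*Protocol article*

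**What the plan says.** The Design section of the protocol article describes a "double-blind, randomized, crossover clinical trial with two arms". Testing is the examiner's task: "Evaluations will be conducted pre- and post-training by the study examiner". On masking, the text is direct: "The examiner will be blind to the allocation of participants".

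The same section then describes how participants learn which platform to use. Someone else prepares the information: "A study researcher will create a letter with the information of the intervention to be performed", with GNPT and ictus.online given as the two possibilities, and that person "will place it in a sealed envelope". The handover, however, falls to the examiner: "The examiner will deliver the sealed envelope to each participant when the first and the third neuropsychological examinations (A1 and A3) take place".

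The section does not place the handover after the day's testing, and it does not say where the envelope is to be opened.

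**The concern.** A seal protects the examiner only until the participant breaks it, and the participant has to break it to know which platform to use. Handing the envelope over at the testing visit makes the assessor's presence the natural setting for opening it, reacting to it or asking what it means. The participants are recruited because they have impaired attention, memory or executive function, so a question to the person who gave them the letter is foreseeable.

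At stake is the masking of the performance-based primary outcomes. An examiner who knows the sequence can, without intending to, vary encouragement, pacing, prompting or borderline scoring between the GNPT and sham periods. The self-report and informant ratings are not part of this point. They are completed by people who may know the platform anyway, whoever delivers the letter.

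**Working it through.** No arithmetic decides this point, so the check sets the provisions of the article side by side.

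1. **Who must stay blind.** The examiner is the one named role that the article states to be blind to allocation. The researcher who randomises is described as blind to the assessment procedure, which is a different thing. The analyst is described as external to the study, not as blind.

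2. **Who carries the letter.** The examiner, at two of the five assessments. With the planned 40 participants this is 40 × 2 = 80 handovers.

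3. **What happens after the first handover.** The examiner's further contacts are A2, A3, A4 and A5. A2 and A4 are the post-training assessments. If the envelope is opened before testing on the day, the A1 or A3 testing is also affected. Under Statistical analysis, A3 is the baseline and A4 the endpoint of group B's GNPT contrast, so a disclosure before A3 testing could touch both ends of it.

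4. **What one disclosure reveals.** There are two sequences: group A takes GNPT then sham, and group B takes sham then GNPT. Knowing the platform in either period fixes the sequence, and so the platform in the other period.

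5. **Which primary outcomes depend on the examiner.** Under Primary outcome measures, the performance-based tests are CPT-II, the Rey Auditory Verbal Learning Test, Digit Span forward, PMR, Digit Span backward and Letter-Number Sequencing. Only CPT-II is described there as computerised. I take the other five of the six to be administered in person by the examiner, because the examiner conducts the evaluations. Those five make up the whole of the memory composite (Rey sub-scores and Digit Span forward) and the whole of the executive composite (PMR, Digit Span backward, Letter-Number Sequencing). Two of the three composite indices therefore rest on the examiner's conduct of the tests.

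6. **Whether the handover needs the examiner.** It does not. A study researcher already writes the letters and knows their content. Under Participants, the team already plans to reach people by post, e-mail and telephone.

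The provisions can all be followed together, so there is no formal contradiction. The allocation of tasks nonetheless gives the blinded role the duty most likely to lead to disclosure, although another role could do it.

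**The case against.** The strongest defence is that the procedure is uniform. Every participant in both groups receives a sealed envelope at the same two visits, from an examiner who neither wrote the letter nor is said to read it. Delivery therefore carries no information. This stands: a reader might infer that the plan's own procedure breaks the blind or contradicts the statement that the examiner is blind, and the text supports neither.

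A reader might also infer a second leak from the way GNPT is configured, since "The neuropsychological assessment done at A1 (for group A) and A3 (for group B) will be used to establish the cognitive profile" and "The examiner from the study will perform the initial neuropsychological assessment". The document does not support that inference. A study researcher stores the results in the platform, all five assessments are planned without distinction by group, and no request to the examiner that depends on the group is described. Which visit feeds the profile is visible to the researcher, not the examiner.

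Third, a journal article leaves operational detail to the full protocol, and instructions on opening envelopes or on non-disclosure may be there. That is fair for the missing instructions, which are no finding by themselves. It does not answer the point, because the article positively assigns the handover to the examiner.

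Fourth, much of the risk of unmasking comes from conversation at later visits, whoever delivers the letter. Tests such as Digit Span and word recall also leave limited room for judgement in scoring. Both are true and limit what the change can achieve. They do not justify adding two avoidable occasions for disclosure.

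**Conclusion.** The point holds as an avoidable risk to the assessor blind. It is a modest procedural weakness in an exploratory pilot, and correcting it would be a cheap improvement.

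Its size cannot be stated. The documents give no rate at which participants disclose their platform and no estimate of how far an unmasked examiner would shift these tests. Any percentage would rest on an invented rate. What can be stated is the reach: up to two handovers per participant, and two of the three composite indices dependent on the examiner.

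The conclusion rests on two assumptions: that the memory and executive tests are given in person by the examiner, and that no unseen document moves the opening of the envelope away from the examiner. If the full protocol does the latter, most of the concern falls away.

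Two further readings go too far. A reader might call the examiner's blind the only blinding the trial claims, but the trial is labelled double-blind and the sham has an interface similar to GNPT's. A reader might also conclude that the performance outcomes have lost their protection. The text shows an exposure to possible disclosure, not a loss of the blind.

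**What to change.** Replace the handover by the examiner. The study researcher who prepares the letters sends each participant the letter and login details by post or e-mail, once testing at A1 and again at A3 is complete, in the same way for both groups. The examiner has no part in this step.

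Add one instruction: participants and their next-of-kin are asked not to mention the platform or its content to the examiner, with a reminder when each later assessment is booked. This addresses the disclosure at later visits that moving the handover cannot prevent.

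Optionally, the examiner records a guess of the sequence at A2 and at A4, after scoring is finished. This makes the blind checkable, which is useful in a pilot meant to inform a full-scale study.

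**Cost.** A procedural amendment with no extra staff and no extra visits. The letter reaches the participant shortly after the visit instead of at it, which may delay the start of each period by a day or so. The optional guess adds one item to two assessment forms.
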